### Ethical Considerations

We adhered to the Declaration of Helsinki to ensure that the rights, integrity, and confidentiality of the respondents are strictly protected. All respondents signed consent forms before being interviewed. For this interventional study, we received human ethics approval from the Human Ethics Committee of Nusa Cendana University Kupang ENT Province Indonesia (ethics ID: 42/UN15.21/KEPK/2024) as shown in Multimedia Appendix 2. All respondents who participated in this study were involved voluntarily without compensation in the form of material; however, they received additional knowledge about malaria. Data obtained from this study will be strictly kept by the principal investigator, and no personal respondent information will be shared during the dissemination of the study results. The research team secured official permission letters from relevant authorities at the provincial, district, subdistrict, and village levels to conduct the study within the designated areas. Written consent forms were collected from all participants participating in this study.

### Dissemination

The findings of this interventional study will be disseminated through national and international conferences and published in peer-reviewed journals.

## Results

The time frame of the project is presented in Table 1.

**Table 1 table1:** Timeline of research phases.

Research phases	January-May 2024	June-July 2024	August 2024-January 2025	February 2025	March 2025-December 2026
Questionnaire and question guide development	✓	—^a^	—	—	—
Ethics approval	—	✓	—	—	—
Training of field workers	—	✓	—	—	—
Household surveys for pretest data	—	—	✓	—	—
Data entry	—	—	✓	—	—
Data analysis	—	—	✓	—	—
Manuscript preparation and submission	—	—	✓	—	—
Intervention in 13 villages	—	—	✓	—	—
Household surveys for posttest data	—	—	—	✓	—
Data entry	—	—	—	—	✓
Data analysis for the final outcome	—	—	—	—	✓
Manuscript preparation and submission	—	—	—	—	✓

^a^Not applicable.

Primary data collection for the baseline survey was conducted between August 2024 and September 2024. A total of 894 rural adults participated in face-to-face interviews in both the intervention and control groups. These participants were drawn from 25 villages across East Sumba District. The intervention commenced in the last week of August 2024 and concluded in the second week of January 2025. The project is currently in the process of drafting multiple research papers, which will be submitted for publication in peer-reviewed journals to disseminate the findings. This study was funded by the Directorate General of Higher Education, Ministry of Education and Culture of the Republic of Indonesia (main contract number: 073/E5/PG.02.00.PL/2024) on June 11, 2024, and an extension contract number from the Research Center of Nusa Cendana University Kupang ENT Province (contract number: 448/UN15.22/SP2H/PL/2024) on June 12, 2024.

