**Methods:**

This study used a cluster-assigned quasi-experimental design with pretest and posttest assessments in control and intervention groups. The control group, consisting of 12 villages, received malaria education integrated into routine health services provided by local health centers. The intervention group, comprising 13 villages, received the same education as the control group, in addition to a malaria campaign conducted once a week for 20 weeks. Before and after the campaign, a household survey was conducted to assess behavioral aspects of malaria, including general knowledge of malaria, AMTSB, and malaria prevention measures knowledge and practice. Improvement in the malaria awareness index, AMTSB, good level of malaria prevention measure knowledge, and good level of malaria prevention measure practice will be determined based on the difference scores for each index before and after the intervention in both groups. The chi-square test will be used to assess score differences. Binary logistic regression analysis will be conducted to identify key risk factors associated with changes in each index.

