First, the research team met with the subdistrict head and village leaders in the 2 selected subdistricts designated as the experimental areas. After obtaining their approval, the research team recorded a campaign message delivered by each subdistrict leader. The campaign content, developed by experts in malaria-related behavior, mathematical modeling, and rural development, included the main symptoms of malaria, prevention strategies, and the appropriate treatment-seeking behavior for suspected malaria cases. During the campaign, the subdistrict head occasionally emphasized key points in the local language to improve comprehension. The recorded message was then combined with a locally popular song to enhance engagement. The final recording was 15 minutes long. Second, 6 health promotion staff members from Baing and Mahu Public Health Centers were selected as RAs to play the recording. The recording was broadcast using loudspeakers to ensure wide community outreach. Third, the RAs played the recorded message once per week for 20 weeks in the 13 intervention villages. The intervention started in the fourth week of August 2024 and concluded in the second week of January 2025. In each selected village, the intervention was conducted in 4 different locations per week to ensure that all community members were reached. The principal investigator maintained weekly communication with the RAs to ensure that the intervention was being conducted properly. Over the 20-week intervention period, the research team monitored implementation by visiting the experimental villages once a month for 5 months.

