The third outcome variable in this study is improvement in good MPMK. This improvement will be demonstrated if the percentage of the rural population with good MPMK after the intervention is higher than before the intervention. A good level of MPMK is defined as the ability to correctly answer at least one-half of the total questions in the MPMK section, as indicated in previous studies [41,59]. The level of MPMK will be assessed before and after the intervention in both the intervention and control groups.

The fourth outcome variable is the use of bed nets during the dry season in high malaria-endemic settings. Community behaviors regarding bed net use may exhibit seasonal variations, as individuals may adjust their practices depending on weather conditions [71]. This outcome will be assessed based on the participants’ self-reported responses to a survey question asking whether they slept under a bed net the night before the survey.

The fifth outcome variable in this study is the variation in the use of a bed net in the dry and wet seasons. The literature indicates that bed net use might fluctuate based on seasonal weather conditions, as individuals adapt their malaria prevention behaviors accordingly [71,72]. This malaria awareness campaign began at the end of August 2024, during the dry season, and concluded in the second week of January 2025, which corresponds to the wet season in the study area. The study will examine seasonal differences in bed net use by analyzing responses to 4 key questions from the malaria prevention practice section of the questionnaire. The disparity in bed net use between dry and wet seasons will be assessed for both the intervention and control groups.

The sixth outcome variable in this study is improvement in good MPMP. Improvement will be demonstrated if the percentage of the rural population practicing good MPMP after the intervention is higher than before the intervention. A good level of MPMP is defined as the ability to correctly answer at least one-half of the total questions in the MPMP section, as indicated in a previous study [73,74].

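### The baseline survey is dated into September 2024 but the campaign began in late August, so some intervention-village pretests may follow first exposure

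*Protocol article*

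**What the plan says.** The protocol article gives these dates and this order:

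- **Baseline survey (Results):** "Primary data collection for the baseline survey was conducted between August 2024 and September 2024".
- **Campaign (Results, same paragraph):** "The intervention commenced in the last week of August 2024 and concluded in the second week of January 2025". Phase III (Intervention Stage) repeats it: "The intervention started in the fourth week of August 2024 and concluded in the second week of January 2025". Outcome Variables agrees: "This malaria awareness campaign began at the end of August 2024, during the dry season".
- **Intensity (Phase III):** "the RAs played the recorded message once per week for 20 weeks in the 13 intervention villages".
- **Stated order (Abstract, Methods):** "Before and after the campaign, a household survey was conducted to assess behavioral aspects of malaria". The phase descriptions follow the same order, with baseline as Phase II and the intervention as Phase III.
- **Who was interviewed at baseline (Results):** "A total of 894 rural adults participated in face-to-face interviews in both the intervention and control groups". Dates are not split by arm or village.
- **Use of the pretest (Abstract, Methods):** improvement "will be determined based on the difference scores for each index before and after the intervention in both groups".

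Table 1 does not settle the order. It puts the pretest surveys and the intervention in the same column, August 2024 to January 2025.

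**The concern.** In a non-randomised pretest/posttest design the pretest has to be free of the intervention. Here the two calendar windows overlap, and the article still describes the survey as coming first.

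The recorded message covers symptoms, prevention and treatment-seeking, which is largely what the awareness index tests. A respondent in an intervention village who was interviewed after the first broadcasts may already score higher. Control villages did not receive the campaign, so this would lift the baseline in one arm only. The intervention arm's pre/post change would then be too small, and so would the difference in change between arms. Several primary outcomes are judged on such differences.

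**Working it through.** **Step 1. Is the late-August start a slip?** Twenty weekly broadcasts span 19 × 7 = 133 days from first to last.
- From 26 August 2024, 133 days lead to 6 January 2025, and week 20 ends on 12 January. This matches the stated end in the second week of January.
- If the campaign had waited for a baseline ending on 30 September and begun on 1 October, the 20th broadcast would fall on 11 February 2025. This contradicts the stated end.

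The article's own 20 weeks and end date therefore support the late-August start.

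**Step 2. How long is the overlap?** The article gives no exact days, so a range is needed. Assumptions: a campaign start between 22 and 31 August, and three possible last days for the baseline survey. Overlap in days = last baseline day − campaign start + 1. Broadcasts by then = whole weeks elapsed + 1.

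| Baseline ends (assumed) | Overlap, days | Broadcasts by then, of 20 |
|---|---|---|
| 1 September | 2-11 | 1-2 |
| 15 September | 16-25 | 3-4 |
| 30 September | 31-40 | 5-6 |

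Example: from 22 August to 30 September is 39 days, so the overlap is 40 days, with 5 whole weeks elapsed and 6 broadcasts.

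**Step 3. Could staggered village starts remove the overlap?** Only for the first days of September. If the second week of January ends on 14 January and each village received all 20 weekly broadcasts, the latest possible first broadcast is 14 January − 133 days = 3 September 2024. On those assumptions, an intervention-village baseline interview after about 3 September followed exposure.

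**Step 4. What would exposed pretests do to the estimate?** Let Δ be the full campaign effect, f the share of intervention-arm baseline interviews that were exposed, and g the share of Δ those respondents had already reached. The intervention baseline rises by f × g × Δ, so the estimated effect is Δ × (1 − f × g). The control baseline does not move, so the difference in change shrinks by the same amount.

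The article gives neither f nor g. For assumed values:
- f = 0.25, g = 0.10: f × g = 0.025. A true gain of 15 points (illustrative) appears as 14.6.
- f = 0.50, g = 0.25: f × g = 0.125. It appears as 13.1.
- f = 0.75, g = 0.50: f × g = 0.375. It appears as 9.4.
- f = 0 (all intervention villages surveyed before their first broadcast): no shrinkage.

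**The case against.** The best defence is that month-level dates pooled over 25 villages do not disprove the stated order within any one village. The baseline included 12 control villages. If the field teams finished the 13 intervention villages first and used September for the controls, every intervention pretest would be clean. This stands as a possibility, and it is why exposure of individual pretests cannot be asserted. But the article does not say it happened, and it would mean that baseline timing differed by arm.

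Three stronger readings are tempting, and the article does not support them:

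- **That the survey filled all of September.** The text gives only the two months; fieldwork could have ended in the first days of September.
- **That the claim of a survey before the campaign is shown to be false.** The dates contradict it as written, but surveying the intervention villages first would rescue it for the arm that matters.
- **That most pretests were exposed and the effect could be halved.** Even interviewing from 1 August to 30 September with a 26 August start would put 36 of 61 days (59%) after the start, but neither the even pace nor the full two months is stated. Even then, mean exposure over those 36 days would be (7 × (1+2+3+4+5) + 6) / 36 = 3.1 broadcasts. That is about 15% of 20, so if the effect grew in proportion to broadcasts the shrinkage would be about 0.59 × 0.15 = 9%. Halving would need half the pretests exposed and the whole 20-week effect already reached.

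Two further points stand. A between-group comparison of posttest results alone, which Statistical Analysis also allows for, does not use the pretest. And for a beneficial campaign the bias is towards no effect, so it would not create a false positive.

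It can also be said that village-level dates and exclusion rules belong in a fuller document. That is fair for the rules. It does not answer the date conflict, because the article itself states both dates and an order that they do not support as written.

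**Conclusion.** The concern holds as a contradiction in dates that may affect the pretest. Any September baseline interview postdates the stated campaign start, by up to about 40 days and 6 of 20 broadcasts, depending on when in September the survey ended. The date overlap is firm. Whether any intervention-village pretest was exposed is unknown.

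If some were, the estimated effect is understated by the share exposed times the share of effect already reached: 2.5% to 37.5% over the assumed ranges, and zero if the intervention villages were finished first. The point needs resolving before the final analysis because the pre/post effect estimates rest on this baseline.

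**What to change.** 1. Check each baseline interview date against the first-broadcast date of that village.
2. Report the numbers of baseline interviews before, and on or after, the first broadcast, by arm and village. For control villages, use the overall campaign start as the reference date.
3. Reconcile the Abstract, Phase II, Phase III and Results: state the actual survey and first-broadcast dates, and correct the statements that the survey preceded the campaign where they do not hold.
4. If any intervention-village baseline interviews fall on or after the first broadcast, flag them before the final analysis, which Table 1 schedules for March 2025 to December 2026. Report the pre/post and difference-in-change results with and without them, and name any village that loses most of its baseline.

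The handling should depend on the date check. Excluding exposed pretests outright as the only analysis could remove whole late-surveyed villages and change the village mix between pretest and posttest. Counting them as exposed would pool people who had 1 to 6 broadcasts with people who had 20.

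Cost: a check of existing records, one extra analysis, and, in the restricted analysis, some loss of intervention baseline sample and village balance.

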## Discussion

### Principal Findings

This research endeavors to examine the impact of integrating multiple media into an interventional study designed to influence malaria-related behavioral changes among rural communities. The intervention incorporated local governmental leaders, traditional music, and loudspeaker announcements, recognizing their potential to enhance community engagement and facilitate effective malaria awareness campaigns. Local authorities play a pivotal role in public health initiatives as they serve as trusted figures within their communities and possess extensive experience in mobilizing the local population [63,83]. Furthermore, music has been shown to be a powerful tool for fostering social connection and disseminating health information, particularly in efforts to promote preventive behaviors for infectious diseases [62]. The use of loudspeakers as a communication medium has also been identified as an effective approach for delivering malaria health messages and ensuring continuous information dissemination in rural settings [61]. Moreover, integrating music-based education enhances learning outcomes among populations with low literacy rates [84], making it a particularly effective strategy for engaging rural communities. This is particularly relevant in ENT Province, where high school dropout rates remain a challenge [85,86]. By leveraging these culturally relevant and widely accessible communication methods, this quasi-experimental study has the potential to generate a significant impact on improving the malaria awareness index, AMTSB, knowledge of malaria prevention measures, and practice of malaria prevention measures among rural adults in ENT Province, Indonesia.

Interventional studies have demonstrated a positive impact on improving malaria-related behaviors at the community level across various settings [50,51,55,60,87-89]. In SEA, several interventional studies have shown significant contributions to behavioral change in malaria prevention and treatment [52,61,90,91]. For instance, a study conducted in Northern Myanmar found that loudspeaker announcements delivering malaria prevention and treatment messages over 6 months significantly increased malaria awareness among villagers [61]. Similarly, a school-based educational intervention in India demonstrated a substantial improvement in malaria prevention and control knowledge among students in grades 9 to 12 [90]. In Pakistan, an interventional study targeting pregnant women indicated that the use of LLINs increased significantly following a 12-week health education program [52]. In Bhutan, a community-directed educational intervention on malaria prevention, implemented over 6 months, led to improvements in malaria-related knowledge, attitudes, and prevention practices among rural communities in Sarpang district [91]. In Indonesia, there is a notable gap in interventional studies focused on malaria education. Most existing research has been conducted in school settings [60] and is primarily concentrated in the western region of the country [59]. To the best of our knowledge, this is the first study in SEA to investigate the combined impact of local leadership, traditional music, and loudspeaker announcements as intervention media to enhance malaria knowledge, improve prevention practices, and encourage early treatment-seeking behaviors among rural communities affected by malaria.

The data collection instruments used in this study were adapted from a validated questionnaire, with modifications made to ensure ease of administration. The measurement of key variables, including the malaria awareness index, AMTSB, MPMK, and MPMP, was based on standardized indicators from reputable international journals. This methodological approach allows for comparability with national and international studies, enhancing the credibility and applicability of the findings. Consequently, the study’s results will serve as an important reference for guiding malaria health policy in rural Indonesia and supporting the national commitment to achieving malaria elimination by 2030.

Despite its strengths, this study has several limitations. First, village selection was not randomized for the control and intervention groups, which may introduce potential selection bias. However, the allocation strategy ensured that the distribution of villages between study groups was comparable in terms of malaria endemicity, and the intervention was designed to maximize its impact by including all villages within a selected subdistrict. Second, most of the data collected in this interventional study relied on self-reported responses from participants, covering aspects such as general malaria knowledge, symptoms, diagnosis, and prevention measure knowledge. This reliance on self-reported data introduces the potential for recall bias. However, to mitigate this limitation, all MPMP were directly observed by RAs during data collection, improving the reliability of reported behavioral measures.

### Conclusions

This study is expected to provide significant findings to comprehensively investigate the change in behavioral aspects of malaria among rural communities following the implementation of a local wisdom-based malaria intervention. Changes in the malaria awareness index, MPMK, MPMP, disparity in using core prevention measures such as LLINs in 2 different seasons, and malaria treatment–seeking behaviors among rural communities due to the implementation of a local wisdom-based health education campaign will be recognized. These findings will provide evidence-based insights into the effectiveness of locally driven health education strategies in malaria-endemic regions. Therefore, this research will contribute to the development of contextually relevant malaria policies in Indonesia. Furthermore, it aligns with global malaria elimination efforts, supporting Indonesia’s commitment to achieving a malaria-free status by 2030.

## Appendix

Multimedia Appendix 1 The questionnaire for primary data collection in pre and post-test.

Multimedia Appendix 2 Ethics approval of nusa cendana university kupang east nusa tenggara indonesia.

## Abbreviations

AMTSB: appropriate malaria treatment-seeking behavior
ENT: East Nusa Tenggara
LLIN: long-lasting insecticide-treated bed net
MPMK: malaria prevention measures knowledge
MPMP: malaria prevention measures practice
RA: research assistant
SEA: Southeast Asia
SES: socioeconomic status
WHO: World Health Organization
